## Abstract

**Objective:**

Hemolytic disease of the fetus and newborn (HDFN) is a rare and serious immune-mediated condition that can result in poor fetal and neonatal outcomes. During pregnancy, monitoring with middle cerebral artery Doppler ultrasound and intrauterine transfusions (IUTs) are the current standard of care, although intravenous immunoglobulin (IVIg) has been adopted in some centers to attempt to delay the onset of fetal anemia. Significant gaps remain in understanding the safety and effectiveness of current HDFN management, both during pregnancy and in neonates and children. We present the design of the Global Prospective Hemolytic Disease of the Fetus and Newborn Registry (GERANIUM; ClinicalTrials.gov Identifier: NCT07194070), a study that will provide real-world, prospective, longitudinal data on management, clinical course, and outcomes of HDFN from the antenatal period up to 2 years after birth.

**Study Design:**

GERANIUM is a prospective, observational study enrolling alloimmunized pregnant individuals (aged ≥18 years) before 24 weeks of gestational age who are at high risk for HDFN based on previous obstetric history. This study will enroll approximately 175 participants across multiple global sites. Data collected during pregnancy include fetal loss, frequency and severity of HDFN, treatment patterns, as well as effectiveness and adverse outcomes of IUTs and other interventions. Following birth, infants will be followed for the first 2 years of life, with documentation of HDFN sequelae, including treatments, growth, and development. Impact on the parents and children will be assessed using validated participant- and observer-reported outcome measures.

**Conclusion:**

The GERANIUM registry will provide prospective, contemporaneous data on current management of HDFN and associated outcomes.

**Key Points:**

## Introduction

Hemolytic disease of the fetus and newborn (HDFN) is a rare and potentially life-threatening immune-mediated condition caused by maternal alloantibody production due to incompatibility between maternal and fetal blood group antigens.
1
2
3
4
These alloantibodies cross the placenta and bind to fetal red blood cells (RBCs), leading to hemolysis and anemia.
4
5
Rhesus D antigen (Rh(D)) alloimmunization occurs in an estimated 1 to 3 per 1,000 Rh(D)-negative pregnancies despite the availability of Rh(D) immunoprophylaxis.
6
7
Rh(D) incompatibility is the most common cause of severe HDFN, accounting for 64.1% of all HDFN cases.
8
Severe HDFN is rare, and a prior history of severe disease greatly increases recurrence risk in subsequent pregnancies, often with earlier onset due to repeated antigen exposure.
9
10
11
12
Severe disease can lead to fetal hydrops, preterm birth, and, after delivery, complications such as hyperbilirubinemia, kernicterus, and persistent anemia requiring plasma exchange or transfusions.
3
4
13
14
15
16
17
18
If severe fetal or neonatal anemia is not adequately managed, there is a high risk of infant mortality.
3
19

Current standard of care (SoC) in the antenatal setting includes monitoring for fetal anemia using middle cerebral artery (MCA) Doppler ultrasound. If severe anemia is confirmed by cordocentesis in alloimmunized pregnant individuals, intrauterine transfusions (IUTs) of RBCs are performed.
20
21
However, IUT is a surgical intervention associated with both procedural risks and short-/long-term risks to the mother and fetus, including emergency cesarean delivery, premature birth, fetal loss, intrauterine infections, and increased maternal alloimmunization.
14
16
22
23
24
In some centers, intravenous immunoglobulin (IVIg) and plasma exchange are used to delay the onset of anemia and the need for an IUT.
25
26
27
However, prospective data to support the effectiveness of IVIg in this setting are limited, and the need for subsequent IUTs remains.
25
26
28
29
Although diagnostics for identifying Rh(D) alloimmunization have improved over time, many patients require intervention with these prenatal treatments; results from a systematic literature review suggested that IUTs were performed in 13% of pregnancies with a positive anti-Rh(D) screen, and IUT combined with IVIg was administered in 3.2% of Rh(D) alloimmunization cases and 4.3% of Kell alloimmunization cases.
1

The large population-based studies conducted to date have been retrospective analyses.
14
15
18
While these studies have provided valuable insights, significant gaps remain in the availability of data on current HDFN management and outcomes. Most existing evidence reflects experience from specialized settings in limited geographies, which may not be representative of broader clinical practice. In addition, SoC and therapeutic options for HDFN have evolved in recent years, making it essential to capture contemporary, real-world data across diverse settings. Here, we report the design of the Global Prospective Hemolytic Disease of the Fetus and Newborn Registry (GERANIUM), which aims to provide prospective, longitudinal, contemporaneous data on current HDFN interventions and outcomes in a real-world cohort of pregnant individuals and their corresponding fetuses, neonates, infants, and children. GERANIUM will also provide data regarding longer-term outcomes on child development, health-related quality of life (HRQoL), medical resource utilization due to HDFN, and biomarkers. The data derived from GERANIUM may provide evidence to increase scientific knowledge, support the development of evidence-based guidelines, provide context for emerging therapies for HDFN, and inform future research directions.

## Materials and Methods

### Ethics

GERANIUM (ClinicalTrials.gov Identifier: NCT07194070) is currently being conducted in compliance with a prespecified protocol and analysis plan in conformance with applicable regulatory requirements. All participating centers will obtain approval from their respective institutional review boards or independent ethics committees prior to the start of the study at their site. All participants will provide written informed consent before any data collection. Each site will maintain documentation of informed consent in accordance with its local regulations and applicable regulatory requirements.

### Participants

Pregnant individuals aged ≥18 years, with an estimated gestational age of up to 24 weeks, and with evidence of alloimmunization in the current pregnancy, along with an antigen-positive fetus corresponding to the current maternal alloantibody, may be enrolled (
Table 1
). Eligible participants are required to have a history of alloimmunization in a previous pregnancy that resulted in HDFN, demonstrated by ≥1 of the following: fetal anemia diagnosed by MCA Doppler ultrasound, received ≥1 IUT, fetal hydrops, stillbirth with fetal or placental pathology indicative of HDFN, neonatal exchange transfusion, neonatal simple transfusion, neonatal hyperbilirubinemia, or positive direct antiglobulin test in the neonate. Individuals who are participating in an interventional trial of an investigational agent or who are at risk for HDFN due to ABO incompatibility alone are excluded.

**Table 1 TB25nov0731-1:** Eligibility criteria

**Inclusion criteria**
• Pregnant individuals aged ≥18 years • Pregnant with an estimated gestational age of up to 24 weeks based on ultrasound dating • History of a previous alloimmunized pregnancy that included ≥1 of the following: ▪ Fetal anemia diagnosed by MCA Doppler ultrasound ▪ Received ≥1 IUT as a result of HDFN ▪ Fetal hydrops ▪ Stillbirth or fetal demise with fetal or placental pathology indicative of HDFN ▪ Neonatal exchange transfusion due to HDFN ▪ Neonatal simple transfusion due to HDFN ▪ Neonatal hyperbilirubinemia due to HDFN ▪ Positive DAT in neonate • Documented presence of maternal alloantibody based on local laboratory results during current pregnancy • Evidence of an antigen-positive fetus corresponding to the current maternal alloantibody: ▪ Fetal antigen status confirmed by cffDNA, or ▪ Fetal antigen status confirmed by amniocentesis, or ▪ Paternal genotype confirmed • The pregnant participant or legally acceptable representative must provide informed consent (per local regulations or ethics committee requirements) for the collection and use of their medical data and the medical data for their corresponding fetuses/neonates/infants/children • The pregnant participant agrees to sign the Release of Medical Information Form or equivalent document, according to local regulation, by all persons who are required to give consent, thereby permitting the participant's health care provider(s) and pediatric health care providers to be contacted for medical information
**Exclusion criteria**
• Active participation in an interventional trial of an investigational agent • At risk for HDFN due to ABO being the sole alloimmunization antigen in the current pregnancy (i.e., ABO plus another antigen is permissible)

Abbreviations: cffDNA, cell-free fetal deoxyribonucleic acid; DAT, direct antiglobulin test; HDFN, hemolytic disease of the fetus and newborn; IUT, intrauterine transfusion; MCA, middle cerebral artery.

### Study Design

GERANIUM is a global, prospective, observational, longitudinal, non-interventional registry of pregnancies affected by HDFN. Data will be collected from eligible pregnant participants during pregnancy from enrollment (on or before 24 weeks of gestational age) and for 2 years after delivery, and from their infants for 2 years after birth (
Fig. 1
). Participants will be recruited from medical centers that routinely diagnose and manage pregnant individuals at risk for HDFN over a period of approximately 5 years. All treatment and clinical management will be conducted following local practice and regulations, as determined by the principal investigator or treating physician. No treatment will be provided by the sponsor as part of this study, and participants will not be discontinued from the registry if they receive any specific interventions, except for an investigational agent received as part of a clinical trial. No study visits, clinical assessments, or procedures will be required.

**Fig. 1 FI25nov0731-1:**
[figure not shown]
GERANIUM registry study design. HCP, health care professional; HDFN, hemolytic disease of the fetus and newborn; MFM, maternal–fetal medicine; OB-GYN, obstetrician-gynecologist; ObsRO, observer-reported outcome; PRO, patient-reported outcome.

### Data Collection

At enrollment, data will be collected from the medical records or participant reports. These data will include demographic characteristics, medical and obstetric history, history of HDFN, diagnosis of HDFN, non-HDFN pregnancy complications, comorbidities, treatments, procedures, adverse outcomes, and fetal assessments.

Antenatal data will be collected retrospectively at enrollment and prospectively after enrollment and will include diagnosis of HDFN, date of HDFN diagnosis, non-HDFN–related pregnancy complications, fetal assessments, HDFN treatment use and patterns, and treatment-related adverse outcomes. HDFN treatments include IUT, IVIg, and plasma exchange as a result of HDFN. Biomarker data, including alloantibody titers and cell-free fetal DNA, may be recorded during routine blood draws. If available, umbilical and uterine artery flow measurements using MCA Doppler will be recorded. In the case of a multifetal pregnancy, data will be collected for each fetus. All clinical assessments will be at the discretion of the physician, depending on the presence and severity of HDFN symptoms.

Pregnant participants will be asked to complete patient-reported outcome (PRO) and observer-reported outcome (ObsRO) assessments to evaluate HRQoL, anxiety and stress, the impact of HDFN on adult family members or partners, and infant/child well-being (
Fig. 1
). All PRO and ObsRO assessments will be voluntary. Medical resource utilization will be documented, including hospitalizations, medical care encounters (emergency room, outpatient, and inpatient), diagnostic tests and procedures, and medications.

At birth, data collected will include gestational age at delivery, mode of delivery, placental evaluation, birth weight, sex, Apgar score at 1 and 5 minutes, neonatal laboratory evaluations at birth, neurodevelopmental assessments, and perinatal complications (including preterm premature rupture of membranes, birth asphyxia, hypoxic–ischemic encephalopathy, and fetal death).

During the postnatal period, information will be collected regarding infant health care resource utilization (e.g., hospitalizations, length of hospital stay, length of intensive care unit stay, rates of emergency department outpatient visits, urgent care and outpatient visits for HDFN parental participants), adverse outcomes related to SoC or concomitant medications, clinical laboratory evaluations (e.g., bilirubin level, platelet count, leukopenia, thrombocytopenia, maximum ferritin), treatments (e.g., phototherapy, IVIg, exchange and simple transfusions, erythropoietin treatment), outcomes (e.g., hyperbilirubinemia, necrotizing enterocolitis, respiratory distress syndrome, sepsis, cerebral injury, kernicterus, major birth defects, assisted feeding type, mortality). Growth and neurodevelopmental outcomes will be collected up to 2 years of life among all liveborn infants, with parent or caregiver permission required for formal enrollment and neurodevelopmental assessments of their child in the study. The modified Neonatal Morbidity and Mortality Index (mNMMI) will be assessed to categorize the severity of outcomes.
30
After hospital discharge, growth and development (e.g., height, weight, head circumference) and neurodevelopmental assessments (Bayley scales) will be collected for up to 2 years. During this period, comorbid conditions will be documented, and health care resource utilization outcomes will be documented.

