### Study Endpoint

A listing of study endpoints is provided in
Table 2
. The primary endpoint of the study is the proportion of pregnancies in participants at risk for HDFN receiving SoC that do not result in fetal loss (due to any reason), IUT, fetal hydrops, or neonatal death (due to any reason) during the neonatal period. Key secondary endpoints include the severity of HDFN, measured using a composite severity index, timing of first IUT or fetal hydrops, number of IUTs received, and risk of mortality and morbidity in neonates born to participants at risk for HDFN using the mNMMI.

**Table 2 TB25nov0731-2:** Study objectives and endpoints

Primary objective	Primary endpoint
To evaluate the risk of anemia in fetuses and neonates of pregnant participants who are at risk for HDFN and receiving SoC	Proportion of pregnancies that do not result in fetal loss (due to any reason), IUT, fetal hydrops, or neonatal death (due to any reason) through the neonatal period
Secondary objectives	Key secondary endpoints
To describe the severity of HDFN as measured by a composite severity index in pregnant participants and their neonates/infants at risk for HDFN and who are receiving SoC	The severity of HDFN is measured by a composite HDFN severity index and is defined as: • 5 (fatal): Fetal or neonatal death due to any reason • 4 (severe): Fetal hydrops (in fetus or newborn) or receiving IUT during pregnancy as a result of HDFN, but not 5 (fatal) • 3 (moderate): Neonatal exchange transfusions received as a result of HDFN-related hemolysis and jaundice, but not 4 (severe) or 5 (fatal) • 2 (mild): Neonatal simple transfusions received due to HDFN after birth, with or without phototherapy, but not 3 (moderate), 4 (severe), or 5 (fatal) • 1 (minimal or none): Not 2 (mild), 3 (moderate), 4 (severe), or 5 (fatal) as described above. HDFN requiring phototherapy will be classified in this category
To describe the timing of the onset of HDFN in pregnant participants at risk for HDFN who are receiving SoC	Time to first occurrence of IUT or fetal hydrops
To describe the risk of mortality and morbidity in neonates born to participants at risk for HDFN who are receiving SoC	mNMMI in liveborn neonates

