To describe antenatal management and outcomes in pregnant participants at risk for HDFN who are receiving SoC	Key secondary endpoint: • Number of IUTs received during pregnancy Other endpoints: • Proportion of pregnancies with fetal loss • Proportion of pregnancies with fetal or neonatal death (through the neonatal period) as a result of HDFN • Proportion of pregnancies with fetal hydrops • Proportion of pregnancies receiving IUT during pregnancy • GA at first IUT • Proportion of pregnancies receiving >1 IUT during pregnancy • The proportion of pregnancies receiving IUT or HDFN resulting in fetal demise before GA week 20 ^0/7^ • GA at delivery • Number of IVIg treatments received and dosage, among pregnancies with ≥1 IVIg, GA at first dose administration, and frequency of administration • Number of plasma exchange treatments received and dosage, among pregnancies with ≥1 plasma exchange treatment, GA at first dose administration, and frequency of administration • Any additional treatment for HDFN
Other objectives	Other endpoints
To describe the neonatal management and other outcomes in neonates/infants of pregnant participants at risk for HDFN who are receiving SoC	• Proportion of pregnancies with neonatal death through the neonatal period • Proportion of liveborn neonates with HDFN-related morbidities other than anemia and hyperbilirubinemia/jaundice • Absolute weight and weight changes over time from birth through week 104 in liveborn neonates/infants • Liveborn neonates' length of stay in the neonatal intensive care unit • Proportion of liveborn neonates receiving exchange transfusions for HDFN • Number of neonatal exchange transfusions per liveborn neonate • Proportion of liveborn neonates/infants with simple transfusions for HDFN up to 12 weeks after birth • Number of simple transfusions for HDFN per liveborn neonate/infant up to 12 weeks after birth • Proportion of liveborn neonates with hyperbilirubinemia treated with phototherapy • Number of days of phototherapy received for hyperbilirubinemia per liveborn neonate • Proportion of liveborn neonates/infants receiving IVIg for HDFN treatment

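### The before-20-weeks endpoint counts women enrolled at 20 to 24 weeks, who can contribute an earlier IUT but not an earlier loss of the pregnancy; the primary proportion is affected less, with no fixed direction

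*Protocol article*

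**What the plan says.** All references are to the protocol article.

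- **Entry (Table 1).** A participant must be "Pregnant with an estimated gestational age of up to 24 weeks based on ultrasound dating". No lower limit or common starting week is given. She must also already have a documented alloantibody and "Evidence of an antigen-positive fetus corresponding to the current maternal alloantibody".
- **Consent (Ethics).** "All participants will provide written informed consent before any data collection".
- **Follow-up (Study Design).** Data on the woman are collected "during pregnancy from enrollment (on or before 24 weeks of gestational age) and for 2 years after delivery".
- **Back-filling (Data Collection).** "Antenatal data will be collected retrospectively at enrollment and prospectively after enrollment". The items collected include treatment: "HDFN treatments include IUT, IVIg, and plasma exchange as a result of HDFN".
- **Exclusions (Table 1).** There are two: active participation in an interventional trial of an investigational agent, and ABO as the only antigen. Neither bars a woman who has already had an IUT or whose fetus is already hydropic.
- **Primary endpoint (Table 2).** It is defined as "Proportion of pregnancies that do not result in fetal loss (due to any reason), IUT, fetal hydrops, or neonatal death (due to any reason"). Its window closes when the neonatal period ends.
- **Before-20-weeks endpoint (Table 2, antenatal management, other endpoints).** "The proportion of pregnancies receiving IUT or HDFN resulting in fetal demise before GA week 20" 0/7. No restriction on gestational age at enrollment is attached.
- **Limitations (Discussion).** Selection is described as a choice: more severely affected women may be less inclined to join. The article does not say that a loss before enrollment makes joining impossible.

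**The concern.** Survival of the pregnancy to enrollment is a condition of entry. Whole-pregnancy loss before that point is left-truncated, whereas IUT and hydrops are not if the fetus survives. An endpoint that adds the two together combines components observed in different ways.

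This is sharpest before 20 weeks. A woman enrolled at 22 weeks counts in the denominator, could have had an IUT at 18 weeks, and cannot have lost the pregnancy at 18 weeks. The reported figure then depends partly on when and why women reach a site. The article plans sites in four world regions and hopes the data will give context for emerging therapies. A figure that shifts with referral timing is hard to compare across regions, or with a cohort that enrolls at other weeks.

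**Working it through.** **There is no plan figure to reproduce.** The sample of about 175 is a feasibility number, with no event rate, alpha or power. The mechanism is checked from the text and then sized with assumed inputs.

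**Structure**

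| Enrolled at | Loss of the pregnancy before 20 wk | IUT before 20 wk |
|---|---|---|
| before 20 wk | seen only if after enrollment | seen before or after enrollment |
| 20-24 wk | impossible | seen, by back-filling |
| never, because lost first | not seen | not seen |

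**Input set A (assumed).** Loss in 8%, uniform over weeks 10-20. First IUT in 45%, uniform over weeks 17-34. Entry uniform over 10-24 or 16-24 weeks.

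- IUT before 20 weeks: 0.45 × 3/17 = 7.9%.
- True composite: 1 - 0.92 × (1 - 0.0794) = 15.3%.
- Entry 10-24: a pregnancy destined for loss is still ongoing at entry with probability 5/14. Share enrolled = 0.92 + 0.08 × 5/14 = 0.9486.
  - Observed loss = (0.08 × 5/14)/0.9486 = 3.0% against 8.0%, a fall of about 62%.
  - Observed composite = (0.92 × 0.0794 + 0.08 × 5/14)/0.9486 = 10.7% against 15.3%, a fall of about 30%.
- Entry 16-24: share enrolled = 0.92 + 0.008 = 0.928. Observed loss = 0.008/0.928 = 0.86%. Observed composite = (0.92 × 0.0794 + 0.008)/0.928 = 8.7%, a fall of about 43%.
- Primary, event-free: true 0.92 × 0.55 = 50.6%. Observed 0.506/0.9486 = 53.3% or 0.506/0.928 = 54.5%. If already-transfused women are three times as likely to be enrolled, simulation gives about 49.0% and 47.0%. The range is -3.6 to +3.9 points.

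**Input set B (assumed; 400,000 simulated pregnancies per scenario).** Cohort at risk from 12 weeks. Background loss over weeks 12-24 of 2, 5 or 10%. First IUT at 16-24 weeks in 10%. Loss within 2 weeks of an early IUT in 15%. Later IUT or hydrops 25%. Later loss or neonatal death 5%.

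Entry uniform over 12-24 weeks, no referral effect (true → observed, %):

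| Background loss | Loss <20 wk | Composite <20 wk | Primary event-free |
|---|---|---|---|
| 2% | 1.9 → 0.7 | 6.3 → 5.1 | 62.9 → 63.8 |
| 5% | 3.9 → 1.4 | 8.2 → 5.8 | 61.0 → 62.8 |
| 10% | 7.2 → 2.6 | 11.3 → 6.9 | 57.7 → 61.0 |

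The loss part falls by about 63-64% and the composite by 19-39%. At 5% background loss the IUT part barely moves (4.9 → 4.7).

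- Entry 18-24 weeks: observed composite 4.5-4.7% against 6.3-11.3%; primary +1.4 to +5.2 points.
- Already-transfused women twice as likely to be enrolled: the composite can be overstated (8.1 against 6.3%) or understated (8.3 against 11.3%), and the primary moves by -2.0 to +1.8 points.

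**Scale.** The 95% half-width at N = 175 is 1.96 × √(p(1-p)/175): 7.4 points at p = 0.5 and 6.8 at p = 0.3 or 0.7.

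**Does delayed entry help?** In set B with entry over 12-24 weeks and no referral effect, women event-free at entry joined the risk set at their enrollment week. The estimates were 6.2, 8.1 and 11.2% against true before-20-weeks risks of 6.3, 8.2 and 11.3%. If nobody enters before 18 weeks, they were 2.6-4.1% against 6.3-11.3%: the early risk cannot be recovered.

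**The case against.** - **This belongs in the analysis plan.** The article condenses a protocol and analysis plan that are not shown; estimators, analysis sets and time origins usually sit there. This has force for the primary endpoint. It does not dispose of the before-20-weeks endpoint, because the article itself fixes an entry window to 24 weeks and an event window to 20 weeks, and the two do not fit.
- **The article does not say outright that IUTs before enrollment count.** True; counting them is the natural reading of back-filled antenatal data. If they did not count, women enrolled at 20-24 weeks could contribute nothing to the numerator, so the mismatch would remain.
- **The inputs are invented.** They are. Set A also places every loss before 20 weeks, which maximizes truncation. Both sets count losses of any cause, whereas the endpoint counts only demise from HDFN, so the real fall could be smaller.
- **Selection is acknowledged.** The Discussion covers women who decline, not those who can no longer be enrolled. It also suggests severe early cases may be less likely to join, the opposite of the referral effect assumed above. This is one reason not to claim a direction.

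Stronger readings that the documents do not support:

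- That early losses can never be seen. Losses after enrollment but before 20 weeks are seen in early enrollees, and loss of one fetus in a multifetal pregnancy could be recorded.
- That every endpoint is a crude proportion. Table 2 includes time to first IUT or hydrops, number of IUTs and gestational age at first IUT.
- That the before-20-weeks endpoint falls from 8.0% to 3.0% or 0.86%. Those figures are all-cause loss alone; on the same inputs the composite falls from 15.3% to 10.7% or 8.7%.

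**Conclusion.** The point holds, mainly for the before-20-weeks endpoint. As defined, its demise part is understated and the composite mixes two differently observed components. With entry spread over 10-24 or 12-24 weeks and no referral effect, the assumed inputs give a fall of about 60% or more in the loss part and roughly 20-40% in the composite. Preferential enrollment of already-transfused women could reverse the sign.

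The primary proportion is subject to the same mechanism, at about -4 to +5 points across both input sets. A reader might infer that the primary result is seriously biased in a known direction. The documents do not support that: missing losses push it up, referral because of an IUT pushes it down, and the net shift stays below the half-width of about 7 points. A confidence interval does not reflect this shift, however, and more enrollment would not shrink it.

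The mechanism rests on the text. Every size rests on assumed event rates and enrollment timing, neither of which the documents give.

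**What to change.** 1. **Before-20-weeks endpoint.** Limit it to women enrolled before 20 0/7 weeks. Estimate it on the gestational-age scale with delayed entry from gestational age at enrollment. Show IUTs before enrollment separately.
2. **Primary endpoint.** Keep the proportion and state that it is conditional on an ongoing pregnancy at enrollment. Report it split by whether IUT or hydrops occurred before enrollment, and by gestational age at enrollment. Add a delayed-entry (Aalen-Johansen) sensitivity analysis among women event-free at entry. Removing pregnancies with earlier events from the main analysis would discard early-onset cases, so that exclusion belongs in the sensitivity analysis only.
3. **Limitations.** State that whole-pregnancy losses before enrollment cannot be observed, and that if few women enter early the early risk cannot be recovered by any analysis. State also that delayed entry assumes timing of enrollment is unrelated to later risk among women event-free at entry.

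**Cost.** This is mainly analysis and reporting wording. Gestational age is checked at entry, and gestational age at first IUT and time to first IUT or hydrops are already endpoints. The price is smaller early risk sets and a wider interval for the before-20-weeks endpoint. Under set A with entry over 10-24 weeks, (0.92 × 4/14)/0.9486 = 27.7% of enrolled women, about 48 of 175, would leave its denominator.
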